### **9.2. Withdrawal of Individual participants**

Participants may discontinue the intervention or withdraw from the study for the following reasons:

- At the request of the child's family
- If the investigator considers that a participant's health will be compromised due to adverse events or concomitant illness that develop after entering the study

If a participant withdraws from the study intervention or from further follow-up visits, this should be documented in the participant records and electronic Case Report Form (eCRF) including the reason for withdrawal, whether study data collected up to that point can be used and whether further follow-up can be conducted.

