## **11.2. Phase 2**

Following screening, participants who score in the top 20% of population norms will be contacted by a member of the research team to see if they would like to participate in the full study.. For those that are selected, they will be contacted by phone and a date will be arranged for a member of the research team to visit them at home to complete the first assessment visit. At this stage it will be ascertained whether there are two parents in the family and whether both would like to take part.

This first assessment visit will take approximately 90 minutes with each family. During this visit the research team will provide additional written and verbal information about the study, and will allow participants to ask any questions about the study. The purpose of the study will be explained, as well as the procedures participants will be asked to complete. Participants will be informed that they can withdraw from any aspect of the home visits, and from the overall study at any time. The randomisation process will also be explained, so participants are aware that they will be randomly allocated to one of the two groups.

521 **11.3. Blinding**

522 Researchers assessing study outcomes will be blinded to randomised allocation. Participants (i.e. parents and their  
523 children) will be informed of their randomised allocation. In the event of a severe adverse event the Chief Investigator  
524 will be notified and may be informed of the randomised allocation.

525 **11.4. Randomisation**

526 Randomisation lists (one per site) will be prepared by a statistician using 1:1 allocation (ViPP intervention vs treatment  
527 as usual) and appropriate block sizes and uploaded on to InForm (the study electronic data capture system) prior to the  
528 start of the study. Eligible subjects will be allocated online to the next available treatment code in the appropriate  
529 randomisation list.

530 Randomisation will be stratified by treatment centre and by willingness and availability of both parents to be involved  
531 (versus one only).

532

533 **11.5. Follow-up visits**

534 Follow-up assessments will be undertaken in the family home by research assistants who are blind to treatment  
535 allocation, at a time convenient for the family.

536 Participants will be contacted by the research team prior to the visit time or the first post-treatment assessment and they  

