### **12.2. Severity of Adverse Events**

Severity of AEs will be assessed according to the following definitions:

Mild: Awareness of event but easily tolerated  
 Moderate: Discomfort enough to cause some interference with usual activity  
 Severe: Inability to carry out usual activity, including play for infants and children

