## 12.4. Serious Adverse Events (SAE)

### 12.4.1. Definition of SAE

An SAE is defined as any adverse event that:

- Results in death
- Is life-threatening\*
- Requires hospitalisation or prolongation of existing inpatient's hospitalisation\*\*
- Results in persistent or significant disability or incapacity
- *Is a congenital abnormality or birth defect\*\*\**

\* "Life-threatening" in the definition of "serious" refers to an event in which the participant was at risk of death at the time of the event; it does not refer to an event which hypothetically might have caused death if it were more severe.

\*\* "Hospitalisation" means any unexpected admission to a hospital department. It does not apply to scheduled admissions that were planned before study inclusion or visits to an accident and emergency department (without admission).

\*\*\* "Congenital abnormality or birth defect" will not be applicable for this trial as all participants will be children aged 12 – 36 months.

Medical judgement should be exercised in deciding whether an adverse event/reaction is serious in other situations. Important adverse events/reactions that are not immediately life-threatening, or do not result in death or hospitalisation but may jeopardise a participant, or may require intervention to prevent one of the other outcomes listed in the definition above should also be considered serious.

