### 12.4.2. Reporting of SAEs

Due to the low risk nature of this study, AEs that do not meet the above Seriousness criteria will not be collected during the study.

Rapid reporting of all SAEs occurring during the study must be performed as detailed in SAE reporting instructions. SAEs will be reported via the eCRF within 24 hours of becoming aware of the event. All reported SAEs will be reviewed by the Chief Investigator (or designee) within 2 working days of receiving notification of the SAE report. The SAE review will be recorded on the eCRF.

SAEs will be followed up until they are resolved.

If the investigator becomes aware of safety information that appears to be related to the treatment, involving a participant who participated in the study, even after an individual participant has completed the study, this should be reported to the Sponsor.

725 12.5 Definition of a Serious Adverse Reaction (SAR)

726 A SAR is defined as a SAE that is judged to be related to the trial treatment.

727 **12.6 Definition of Unexpected and Related Serious Adverse Events**

728 A Related and Unexpected Serious Adverse Events is an Adverse Event that is classed as serious, is suspected to

729 be caused by the trial treatment and is unexpected i.e. not listed as an 'expected SAE' in this protocol.

730 **12.6.1 Reporting of Related and Unexpected Serious Adverse Events**

731 All Related and Unexpected Serious Adverse Events will be notified to the Research Ethics Committee (REC)

732 and the Sponsor within 15 days of becoming aware of the event.

733 Follow up of participants who have experienced a Related and Unexpected Serious Adverse Event should

734 continue until recovery is complete or the condition has stabilised.

735 **12.7 Annual reporting of SAEs**

736 Annual safety reporting will be included in the annual progress report sent to the REC, on the anniversary of

737 Ethics approval each year.

738

739 **13. STATISTICAL ANALYSES**

740 **13.1. Sample Size and power considerations**

741 The total sample size will be 300 participants.

742 If losses to follow-up are 20%, this leaves 120 participants per group with follow-up data. We would then have

743 80% and 90% power to detect standardised effect sizes of 0.36 and 0.42 respectively, at the 5% significance

744 level. In addition, we have stated that our analysis will adjust for baseline behavioural score, research centre and

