### 1614 5.3 Safety Variables

1615 There are no obvious adverse events that are expected to be related to the ViPP intervention and the risk to  
1616 participants is believed to be low. We have therefore not specified any particular type of adverse events in  
1617 advance, other than serious adverse events, for routine collection. Information on all serious adverse events  
1618 affecting any family members who are participating in the study (i.e. the child and the one or two participating  
1619 care-givers) will be collected for the duration of the follow-up period, irrespective of the likely connection to the  
1620 intervention. Information on mild to moderate adverse events will be collected only if the event might plausibly  
1621 be attributable to the intervention.

1622 It is important to note that some adverse events (such as incarceration or death of sibling) may be reported  
1623 indirectly, through the process of re-scheduling appointments, for example, rather than directly as an adverse  
1624 event. The database notes columns will be scrutinised prior to analysis in order to identify these. Hospitalisation  
1625 of the child, will be collected via the CASUS form which is designed to collect health care utilisation data for  
1626 the economic analysis.

1627

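### Protocol and SAP contradict each other on whether non-serious adverse events are collected, and neither rule covers a severe, non-serious event related to ViPP-SD

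*Combined protocol and SAP*

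**What the plan says.** Protocol 12.2 grades adverse events as mild, moderate or severe, and defines the top grade by loss of function: "Severe: Inability to carry out usual activity, including play for infants and children". Seriousness is defined separately in 12.4.1 by outcome (death, threat to life, unplanned admission, lasting disability), with a clause for other cases: "Medical judgement should be exercised in deciding whether an adverse event/reaction is serious in other situations".

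Two rules govern collection.

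- Protocol 12.4.2: "AEs that do not meet the above Seriousness criteria will not be collected during the study".
- SAP 5.3: serious events in the child and the participating care-givers are collected whatever their likely cause, and "Information on mild to moderate adverse events will be collected only if the event might plausibly" be due to the intervention.

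For reporting, SAP 6.5 and Table 8.17 show serious events and, in separate rows, other adverse events judged relevant. Both are tabulated by type of event and compared between groups with Fisher's exact test.

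Two further protocol sections refer to adverse events without using the seriousness definition. Section 11.3 reads "In the event of a severe adverse event the Chief Investigator" and goes on to say that this person is notified and may learn the allocation. Section 9.2 lists as one ground for stopping: "If the investigator considers that a participant's health will be compromised due to adverse events or concomitant illness".

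**The concern.** A site that follows the protocol records no non-serious event. A site that follows the SAP records some of them. The analysis plan then reserves table rows for data that the protocol says will not exist.

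The SAP's choice of words adds a second difficulty. It splits events into serious ones and mild to moderate ones, although the protocol's severity scale has a third grade and is independent of seriousness. A child or care-giver who cannot carry out usual activity after a session, without admission and without anyone judging the event serious, falls outside both classes even if the event is plainly related to ViPP-SD.

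What is at stake is how the safety comparison is read. If the rows for relevant non-serious events come out empty or nearly so, a reader cannot tell whether nothing happened or nothing was collected.

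**Working it through.** No arithmetic applies to the collection rules, so they are set side by side for each type of event.

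| Type of event | Protocol 12.4.2 | SAP 5.3 |
|---|---|---|
| Serious, any severity | collected | collected, whatever the cause |
| Non-serious, mild or moderate, plausibly related | not collected | collected |
| Non-serious, severe, plausibly related | not collected | no rule |
| Non-serious, mild or moderate, not plausibly related | not collected | not collected |
| Non-serious, severe, not plausibly related | not collected | no rule |

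The second row is a direct contradiction. The third is a gap: the protocol excludes the event and the SAP does not mention it. The assessment schedules (protocol 11.6, SAP 3.9) do not settle either, because both list only serious adverse events.

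Each other place that might capture an event in the third row was then checked.

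1. *Judgement clause, protocol 12.4.1.* This turns an event into a serious one if it could put the participant at risk or needs intervention to prevent a listed outcome. It covers some severe events, but not one that stops usual activity without posing such a risk.
2. *Reporting to the sponsor, protocol 12.4.2.* Safety information that appears related to treatment goes to the sponsor, with no limit of severity or seriousness. This is a communication and does not by itself create an adverse event record.
3. *Notification of the Chief Investigator, protocol 11.3.* The same applies. It is also unclear whether 'severe' here carries its 12.2 meaning.
4. *Search of the database notes, SAP 5.3.* This looks for events reported indirectly, for example when appointments are rescheduled. It finds only what someone happened to write down.
5. *Reason for withdrawal, protocol 9.2.* This goes into the eCRF, but only for those who stop, and nothing links it to an adverse event record.
6. *SAP 6.5 and Table 8.17.* The rows for relevant events have no severity limit, so a known severe event could be shown. A table can show only what has been captured, however.

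These routes narrow the gap but do not close it.

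Timing limits what can still be changed. SAP 2.0 is dated 7 May 2019, and SAP 3.7 puts the end of recruitment in July 2017. In the visit schedule (protocol 11.7, SAP 3.8) the latest date for session 6, using every upper window, is (28 + 7) + 3 × (14 + 7) + 2 × (21 + 7) = 35 + 63 + 56 = 154 days after randomisation. For a family randomised on 31 July 2017 that is 1 January 2018, about 16 months before SAP 2.0. The schedule is described as a guide, so some sessions may have run later. Even so, a rule changed with this SAP could do little for events during the intervention period.

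**The case against.** The strongest reply is that this is loose wording. In SAP 5.3, 'mild to moderate' comes straight after the sentences on serious events and may simply mean non-serious. Likewise 'severe' in protocol 11.3 may mean serious, since 12.4.2 has the Chief Investigator review serious events. On that reading there is no severity gap. This is possible, but the documents do not say so, and 12.2 gives 'severe' a defined meaning. The contradiction with 12.4.2 remains on either reading.

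A second reply is that the SAP does not in practice confine itself to mild and moderate events. Its examples for the search of the database notes are incarceration and the death of a sibling, and neither is mild. This stands, and it is why the gap is described as one in the collection rules and not as a complete loss of data.

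A third reply concerns withdrawals. An investigator who withdraws someone on the 9.2 ground quoted above has largely made the judgement that renders the event serious under 12.4.1. This also stands. A reader might infer that events ending participation are generally lost, and the documents do not support that. What remains is withdrawal at the family's request, and severe events that do not lead to withdrawal.

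Two stronger readings should also be set aside. A reader might infer that a severe related event is dropped while a mild one is kept. That pairs the protocol's exclusion with the SAP's inclusion: under the protocol the mild event is dropped too, and under the SAP the severe one is unaddressed. A reader might also infer that a severity stratum of Table 8.17 is empty by rule. The table has no severity strata; its rows are by category of event.

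**Conclusion.** The point holds as a contradiction between the two documents, with a gap in coverage alongside it. Protocol 12.4.2 and SAP 5.3 cannot both be followed for mild or moderate events plausibly related to ViPP-SD. No collection rule in either document covers a severe, non-serious, related event.

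Taken literally, the protocol leaves the planned rows for non-serious events in Table 8.17 without collected data, and the SAP leaves out the most intense related non-serious events. The number of events affected cannot be derived from the documents. No efficacy result, power figure or sample size depends on it.

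The conclusion assumes that 'severe' carries its 12.2 meaning wherever it is used and that 'mild to moderate' is meant literally. If both are loose wording, the coverage gap disappears and the contradiction on non-serious events remains. The point should be acted on because it affects how the safety table is read and costs little to put right.

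**What to change.** 1. Reconcile protocol 12.4.2 and SAP 5.3 into one collection rule. In SAP 5.3, replace the reference to mild to moderate events with non-serious adverse events of any severity, and amend 12.4.2 to match.
2. Carry any adverse event already recorded in the eCRF as a reason for withdrawal under protocol 9.2 into Table 8.17, for both arms.
3. Reconcile 'severe' in protocol 11.3 with the definitions in section 12, so that the text shows whether the severity grade or the seriousness definition is meant.
4. State in the trial report which non-serious events were actually collected, and under which rule, so that an empty row is not read as absence of harm. Since most prospective capture is no longer possible, this is the step that helps most.

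The cost is wording in two documents, a check of withdrawal reasons that should already be in the eCRF, a short statement in the report, and a few more adverse event records.

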### 1554 1555 4.2 Safety population

1556 The safety population will be children and their parents/ care-givers who have received at least one intervention  
1557 as part of the ViPP programme, compared to those allocated to the control group who have not received any  
1558 ViPP intervention. Adverse events will be compared between arms according to these safety definitions of  
1559 groups.

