## 1792 6.5 Safety Analysis

1793 A table of serious adverse events and any adverse events considered to be relevant will be produced, by type of  
1794 event and by treatment received.

1795 The table will show numbers of children who have at least one such adverse event of a given type and then  
1796 numbers of families where at least one parent/care-giver is affected by this type of adverse event. Percentages  
1797 (of children/ families) will be calculated and presented. Proportions will be compared between treatment groups  
1798 using Fisher's exact test.

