| For the child: n (% of families)                                                             |                                             |                                                                                     |                                                                             |
| Any Adverse Events that are considered relevant, by category,
giving number of children affected |                                             |                                                                                     |                                                                             |
| Serious Adverse Events, by category, giving number of children
affected                          |                                             |                                                                                     |                                                                             |
| For parents/care-givers: n (% of families)                                                   |                                             |                                                                                     |                                                                             |
| Any Adverse Events that are considered relevant, by category,
giving number of families affected |                                             |                                                                                     |                                                                             |
| Serious Adverse Events, by category, giving number of families
affected                          |                                             |                                                                                     |                                                                             |

1963

1964 9 Index of Supplementary Tables

1965 9.1 Table: Sensitivity Analyses for lack of adjustment for length of follow-up: Primary and Secondary  
1966 Outcomes on Child Behaviour, ITT analysis

| Randomised group                                                               | ViPP Group |           | Control Group |           | Treatment Effect |         |
|--------------------------------------------------------------------------------|------------|-----------|---------------|-----------|------------------|---------|

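### Mild to moderate adverse events enter the data only if plausibly due to ViPP, yet SAP 6.5 and Table 8.17 test them between ViPP recipients and families who never had it

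*Combined protocol and SAP*

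**What the plan says.** **Collection.** SAP 5.3 has two rules. Serious events in the child and the participating carers are recorded without regard to cause; the operative words are "care-givers) will be collected for the duration of the follow-up period, irrespective of the likely connection to the" intervention. For the rest, "Information on mild to moderate adverse events will be collected only if the event might plausibly" be due to the intervention. The section adds a second route for events that come to light indirectly, for instance when an appointment is moved: "The database notes columns will be scrutinised prior to analysis in order to identify these".

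**Groups.** SAP 4.2 takes families with at least one intervention "as part of the ViPP programme, compared to those allocated to the control group who have not received any" ViPP.

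**Analysis.** SAP 6.5: "A table of serious adverse events and any adverse events considered to be relevant will be produced, by type of" event and by treatment received, with proportions compared between groups "using Fisher's exact test". Table 8.17 carries this out. For the child and again for the carers it has a row headed "Any Adverse Events that are considered relevant, by category", with a column for each group and a p-value column.

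**Protocol.** Section 12.4.2 states a different collection rule: "Due to the low risk nature of this study, AEs that do not meet the above Seriousness criteria will not be collected" during the study.

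**The concern.** Whether a non-serious event is recorded depends on whether it can be linked to ViPP. The comparator is defined by having had no ViPP; a control family that did receive some is left out of it. So the condition for being counted is tied to the exposure being compared. The same mild complaint could be entered for a ViPP family and passed over for a control family.

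This could mislead in two directions. A cluster of mild events in ViPP recipients could produce a significant difference with no true excess. An empty or nearly empty row could look like comparative reassurance when no like-for-like comparison had been made. Equal contact and complete follow-up in both arms would not remove the problem, because it comes from the recording rule.

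**Working it through.** **1. Figures in the documents.** There is none for the safety comparison: no expected event rate and no power. The only power statement (protocol 13.1, SAP 3.6) concerns the primary outcome. With 120 per group it claims 80% and 90% power at 0.36 and 0.42 SD. A normal approximation gives 79.6% and 90.2%, and 240/(1 − 0.20) = 300, so the group sizes used below are consistent.

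**2. Inputs.** 150 families per arm (protocol 6); 120 per arm after 20% loss (SAP 3.6); 5% significance level (SAP 6.1), taken as two-sided because the side is not stated. The ViPP safety group is families with at least one session, so 150 is its upper limit.

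**3. Worst case for one row.** With *k* families affected among *n* ViPP families and none among *n* controls, the two-sided Fisher p-value is

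p = 2 × ∏ (n − i)/(2n − i), for i = 0 to k − 1.

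- n = 150, k = 5: 2 × (150/300)(149/299)(148/298)(147/297)(146/296) = 0.060
- n = 150, k = 6: the same product × (145/295) = 0.030
- n = 120: k = 5 gives 0.060 and k = 6 gives 0.029

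So six families (6/150 = 4.0%) in a single category cross the 5% level. Table 8.17 splits events by category and by child or carer. Six families divided three and three over two categories would give p = 0.247 in each row (3/150 v 0/150).

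**4. If control recording is reduced but not absent.** Assume the same true rate in both arms for one category, and let controls have only a fraction of their events recorded. Rates and fractions are assumptions. Exact enumeration with 150 per arm gives these probabilities of p ≤ 0.05 when there is no true difference:

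| Control recording relative to ViPP | Rate 2% | Rate 5% | Rate 10% |
|---|---|---|---|
| 0 | 8.2% | 76.6% | 99.8% |
| 25% | 4.3% | 32.9% | 71.7% |
| 50% | 2.2% | 11.9% | 29.8% |
| 100% | 1.2% | 2.4% | 3.3% |

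At an assumed 5% or 10%, recording half of the control events is enough to take the false-positive probability above 5%. At an assumed 2%, only complete loss does so.

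**5. Is symmetric recording provided for elsewhere?** Neither assessment schedule (protocol 11.6, SAP 3.9) has an item for non-serious events; both list serious events only. No section says how attribution is to be judged in a family that had no ViPP.

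**The case against.** A reader might infer that the control count is zero by construction and the p-value therefore meaningless. The documents do not go that far.

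- The condition is that an event *might plausibly* be due to the intervention. That can be judged by type of event, or by someone who does not know the arm. Protocol 11.5 has follow-up assessments done by blinded research assistants, and control families have those visits too, so a control event could be recorded.
- The search of the database notes has no stated limit to one arm and no stated attribution condition, and SAP 6.5 does not define relevance as having passed the attribution filter.
- The table is by category, so a handful of scattered events would not reach significance, and SAP 5.3 expects low risk.
- Under protocol 12.4.2 the non-serious rows could be empty in both groups.

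All of this stands against a certain zero. It does not restore a fair comparison. Blinded assessors have no scheduled question on non-serious events. The notes search relies partly on rescheduled appointments, and ViPP families have up to six extra sessions to reschedule, so that route may also favour recording in the ViPP group. Parents know their allocation (protocol 11.3). Without a rule for control families, equal recording is possible, but nothing in the plan secures it.

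**Conclusion.** The concern holds for the non-serious rows of Table 8.17. Recording of these events is likely to be lower in the control group, with zero as the strict-reading extreme, so the planned Fisher p-value cannot be read as evidence for or against harm.

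The threshold of six affected families against none is a worst case. It assumes one event category, no control events recorded, about 150 (or 120) families per group and a two-sided test. The false-positive probabilities rest on assumed event rates and recording fractions and show sensitivity only; they do not predict what this trial will find.

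It would be wrong to extend the point to the whole safety analysis. Serious events are collected in both arms whatever their cause, so this filter leaves their comparison intact. The efficacy analyses are unaffected. Separately, SAP 5.3 and protocol 12.4.2 contradict each other on whether any non-serious events are collected.

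**What to change.** In SAP 6.5 and Table 8.17:

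1. Restrict the Fisher comparison to serious adverse events.
2. Report the attribution-filtered non-serious events descriptively, as counts and a listing with no between-arm p-value, and state the collection rule in a footnote.
3. Reconcile SAP 5.3 with protocol 12.4.2, so that the reader knows whether non-serious events were collected and under which rule.

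This needs SAP wording and a table-shell edit, with no new data. The downside is the loss of one formal test on ancillary rows. Uniform prospective questioning at 5 months was not open to this SAP version: recruitment ended in July 2017 (SAP 3.7) and version 2.0 is dated 7 May 2019, after the 5-month visits were due.
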